# Exploring the utility and acceptability of Faecal immunochemical testing (FIT) as a novel intervention for the improvement of colorectal Cancer (CRC) surveillance in individuals with lynch syndrome (FIT for lynch study): a single-arm, prospective, multi-centre, non-randomised study

**DOI:** 10.1186/s12885-022-10217-y

**Published:** 2022-11-07

**Keywords:** Lynch syndrome, Colorectal Cancer surveillance, Bowel Cancer surveillance, Mismatch repair deficiency, Faecal immunochemical testing (FIT), Microbiome

## Abstract

**Background:**

Lynch Syndrome (LS) is an inherited cancer predisposition syndrome defined by pathogenic variants in the mismatch repair (MMR) or *EPCAM* genes. In the United Kingdom, people with LS are advised to undergo biennial colonoscopy from as early as 25 until 75 years of age to mitigate a high lifetime colorectal cancer (CRC) risk, though the consideration of additional surveillance intervention(s) through the application of non-invasive diagnostic devices has yet to be longitudinally observed in LS patients. In this study, we will examine the role of annual faecal immunochemical testing (FIT) alongside biennial colonoscopy for CRC surveillance in people with LS.

**Methods/design:**

In this single-arm, prospective, non-randomised study, 400 LS patients will be recruited across 11 National Health Service (NHS) Trusts throughout the United Kingdom. Study inclusion requires a LS diagnosis, between 25 and 73 years old, and a routine surveillance colonoscopy scheduled during the recruitment period. Eligible patients will receive a baseline OC-Sensor™ FIT kit ahead of their colonoscopy, and annually for 3 years thereafter. A pre-paid envelope addressed to the central lab will be included within all patient mailings for the return of FIT kits and relevant study documents. A questionnaire assessing attitudes and perception of FIT will also be included at baseline. All study samples received by the central lab will be assayed on an OC-Sensor™ PLEDIA Analyser. Patients with FIT results of ≥6 μg of Haemoglobin per gram of faeces (f-Hb) at Years 1 and/or 3 will be referred for colonoscopy via an urgent colonoscopy triage pathway.

16S rRNA gene V4 amplicon sequencing will be carried out on residual faecal DNA of eligible archived FIT samples to characterise the faecal microbiome.

**Discussion:**

FIT may have clinical utility alongside colonoscopic surveillance in people with LS. We have designed a longitudinal study to examine the efficacy of FIT as a non-invasive modality. Potential limitations of this method will be assessed, including false negative or false positive FIT results related to specific morphological features of LS neoplasia or the presence of post-resection anastomotic inflammation. The potential for additional colonoscopies in a subset of participants may also impact on colonoscopic resources and patient acceptability.

**Trial registration:**

Trial Registration: ISRCTN, ISRCTN15740250. Registered 13 July 2021.

## Background

Lynch Syndrome (LS) is an inherited cancer predisposition disorder associated with an increased lifetime risk of gastrointestinal, gynaecological, and other cancers. It is characterised by the presence of pathogenic variants in the mismatch repair (MMR) genes, *MLH1, MSH2, MSH6, PMS2*, or a deletion in *EPCAM*, which regulates *MSH2* gene expression [1].

Colorectal cancer (CRC) is the most common of known LS-associated cancers, with cumulative incidence which is gene-specific and shown to steadily increase by age. By age 70 years, pathogenic variants in *MLH1* and *MSH2* convey a 46 and 35% risk of CRC development, respectively, despite colonoscopic surveillance, whereas those with pathogenic variants in *MSH6* or *PMS2* observe markedly lower cumulative incidence rates by the same age: *MSH6* (20%) and *PMS2* (0-1%) [2]. The varied risk observed between LS-associated pathogenic variants within the MMR pathway may be a reflection of both gene-specific risk, and/or gene-specific effectiveness of colonoscopic surveillance, especially in *PMS2* carriers [3].

In considering the respective cumulative lifetime risks of CRC, the effectiveness of routine surveillance is therefore paramount to ongoing clinical care and management in this patient population [4]. In the UK, surveillance via colonoscopy is recommended at least once every 2 years (biennially) for LS patients. For LS patients with pathogenic variants in *MLH1* and/or *MSH2*, biennial colonoscopic surveillance is recommended to begin at age 25, whereas individuals with pathogenic variants in *MSH6* and/or *PMS2* are advised to commence colonoscopic surveillance at 35 years of age. Colonoscopic surveillance stops at 75 years of age for all LS patients, regardless of MMR pathogenic variant [5].

Though a steady increase in survival has been observed in recent years for LS patients with a prior history of CRC [6], the requirement of up to 25 colonoscopies throughout one’s lifetime is both invasive and resource intensive. Moreover, recent literature has challenged current surveillance guidelines following the publication of prospective data which has observed a similar colorectal cancer stage distribution amongst LS patients irrespective of time since their last colonoscopy [2, 7, 8].

### Rationale for current study

Presently, FIT is used as a non-invasive triage tool for referring people for colonoscopic (or other) investigation in asymptomatic patients invited to participate in national bowel cancer screening programmes, as well as in symptomatic patients presenting to primary care with symptoms suggestive of CRC who require urgent colonoscopy [9, 10]. The utility of FIT for the purpose of surveillance in patients with Lynch Syndrome, however, has not previously been formally assessed to our knowledge.

During the COVID-19 pandemic, an emergency national clinical service utilising FIT was implemented by our team for people with LS within England, entitled “*Rapid evaluation of Faecal immunochemical testing (FIT) levels in individuals with a Lynch Syndrome pathogenic variant to determine a revised threshold for colonoscopy in response to the COVID-19 pandemic* (Short Title: “Rapid FIT for Lynch”) [11]. Data from this emergency service has provided important preliminary insights into the design of the research study described in this paper. In this response to the COVID-19 pandemic, eligible LS patients were mailed a FIT kit in lieu of their standard surveillance colonoscopy, which may have been cancelled or indefinitely postponed, as a way of escalating priority of suspected high-risk patients (as defined by having a FIT result ≥10 μg of haemoglobin (Hb) per gram of faeces (f-Hb)).

Overall, an uptake rate of 63.7% was observed (375/588) for those LS patients who had returned their FIT kit to the laboratory for analysis. We also observed earlier diagnoses of CRC in patients whose investigations were escalated after a positive FIT.

Given the acceptable uptake rate of FIT in this LS patient cohort, we believe that a structured programme enabled by longitudinal research with annual FIT alongside biannual colonoscopy is warranted to sufficiently examine the efficacy of FIT as an additive, non-invasive diagnostic modality for the purposes of surveillance in patients with Lynch Syndrome.

### Objectives

#### To evaluate the specificity of FIT in patients with lynch syndrome

The observation of true negative FIT results for participants will be made through the confirmation of no visible advanced adenomas (AA’s) or CRC at time of colonoscopy and subsequent negative (normal) pathology reports for patients with preceding negative FIT results (< 6 μg/g f-Hb).

#### To identify and explore acceptability, views, and preferences of FIT in this patient population

A qualitative assessment of patient baseline questionnaires, which are adherent to a theoretical framework for the acceptability of novel or self-sampling healthcare interventions [12, 13]. This questionnaire will be distributed to patients as part of their baseline (Year 0 (Y0)) mailing.^1^

#### To evaluate the sensitivity of FIT for the detection of CRC in patients with lynch syndrome

The observation of true positive FIT results will be confirmed by the detection of CRC at the time of colonoscopy, and subsequent confirmation via pathology reports for patients with preceding positive FIT results (≥6 μg/g f-Hb).

#### To evaluate the sensitivity of FIT for the detection of advanced adenomas (AA’s) in patients with lynch syndrome

Herein, AA’s are characterised as an adenoma measuring ≥10 mm, containing a villous component, or displaying high grade dysplasia [14].

#### To examine and characterise the faecal microbiome of patients with lynch syndrome

The faecal microbiome of participants who have opted in for additional research will be characterised. 16S rRNA V4 gene sequencing will be performed on residual bacterial DNA from archived FIT samples and results analysed according to colonoscopy outcome.

Future amended versions of this protocol may also allow for the assessment of cancer-associated genetic changes in human DNA from collected stool, which has the potential to improve the accuracy of microbiome-based tests.

#### To observe the incidence of interval CRCs for lynch syndrome patients with negative FIT results

The rate of potential interval CRCs will be observed in a subset of LS patients with preceding negative FIT results up to the end of the passive follow-up period (Baseline + follow-up years 1-3 + 3 years passive follow-up) for a total of 7 years.

Though the risk of interval CRCs following FIT testing has been previously examined in symptomatic patients [15], interval CRC risk following FIT testing in patients with Lynch Syndrome has yet to be explored.

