### Baseline recruitment

Potential eligible participants will be identified by the local PI and study team of the respective participating NHS Trusts via a i) Lynch Syndrome registry ii) local regional genetics service databases iii) through linked endoscopy clinical records held within their local Regional NHS Trusts and/or iv) through the completion of a reply slip that may be sent from a participating Regional Genetics Service (study site) direct to their LS patients, which shall be sent along with a patient inquiry letter as part of an initial optional patient mailing, as detailed below. Inclusion and exclusion criteria will be verified by the hospital clinical records. Ethically-approved advertisement flyers and patient informational posters will be shared amongst Lynch Syndrome support groups and related networks as an addition strategy to inform eligible patients about the study.

The Research laboratory at the Bowel Cancer Screening South of England Hub (referred to as the “Southern Hub laboratory”), based at the Royal Surrey County NHS Foundation Trust in Guildford, will act as the central laboratory for this study. Participating study sites will email an excel spreadsheet containing patient details by secure nhs.net email patients meeting full inclusion criteria for the study. Southern Hub laboratory research staff will compile baseline mailings (Year 0) for each eligible patient which will be mailed direct to eligible patients within 7-30 days prior to their next scheduled standard of care (SOC) colonoscopy. This specific time frame (7-30 days) was devised by considering FIT kits to be received by eligible patients prior to commencing bowel preparations for colonoscopy, and in considering potential mail delays or delivery disruptions.

Prior to the distribution of a baseline mailing, Southern Hub laboratory research staff will assign a Study ID to each eligible patient which will be recorded within a secure master database internal to the Southern Hub research laboratory and restricted solely to assigned study staff.

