### Post-baseline study years 1-3: contact & mailings

Following active recruitment and baseline period (Year 0), participants will be re-contacted by Southern Hub laboratory research staff via mail on an annual basis for an additional 3 years (Study Years 1-3) after baseline (Year 0). Subsequent mailings for enrolled participants for Years 1-3 will be comprised of the following items and materials: i) a participant post-baseline letter, ii) a participant information sheet, iii) an OC-Sensor™ FIT kit enclosed within a biospecimen bag, iv) a FIT instruction sheet, and a v) return envelope with prepaid postage. Mailing of study materials and FIT kits for study participants at Study Year 2 will be sent ahead of their SOC colonoscopy at this time point (in line with the UK’s LS surveillance guidelines) also within a 7–30-day window (See Fig. 1 and Table 1) .

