### Data collection and planned analysis

Colonoscopy and/or histopathology reports will be requested for all participating individuals who return a FIT kit throughout the duration of the trial (Baseline + Years 1-3) as part of the outcome data required for analysis. After the trial has ended, and dependent on the procurement of additional research funds, we will continue to passively observe a subset of trial participants who had preceding negative FIT results to discern potential incidence of interval advanced colorectal neoplasia (ACN) over the course of 3 years. The study has received written approval from the Research Ethics Committee (REC) of Clinical Research of each participating region (REC Reference: 21/YH/0066).

A secure and encrypted database will be constructed with a unique study ID for each participant and routinely checked for errors. A summary of study variables to be collected are reflected within Table 2.

**Table 2 Tab2:** Study measurements

Participant	
Study ID, DOB^a^, sex, ethnicity, NHS Lynch Syndrome genotype, local PI and participating NHS Trust.	
FIT Data	
Dates of participant mailings sent from the Southern Hub (baseline and years 1-3), FIT results (f-Hb for baseline and years 1-3.	
Clinical^a^	
Date of colonoscopy at baseline and years 1-3 + follow-up years 4-6 for the subset of eligible patients, histological features and staging (where applicable) of biopsied specimen(s) at time of colonoscopy, anastomosis (Y/N), gastrointestinal (GI) comorbidities (Y/N), History of CRC (Y/N), date of CRC (where applicable), prior GI surgery (Y/N), GI surgery type (where applicable), other cancer(s) (Y/N), bowel prep quality, polyp retrieval (Y/N), colonoscopy key performance indicators (KPI) met (Y/N), aspirin use (Y/N), aspirin dosage (where applicable), additional medications (Y/N), additional medication details and dosage (where applicable).	

^a^Data to be collected only for those who return a sample i.e., consent

Both interim and final datasets will be created and analysed within Stata statistical software. The REDCap database and related .csv files will be imported into Stata for final cleaning and analysis.

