#### Objective 6 (exploratory)

The assessment of interval CRC’s will be examined after study end and during the passive follow-up period (Y4-Y7) in a subset of LS patients who had FIT negative results (< 6 μg/g f-Hb) throughout the course of the study (baseline + Y1-Y3).

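### Objective 6 does not separate CRCs and person-time by whether FIT or colonoscopy was the last test, so its rate cannot by itself show the risk after a negative FIT

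*Protocol article*

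**What the plan says.** The interval-CRC item under Objectives states that "The rate of potential interval CRCs will be observed in a subset of LS patients with preceding negative FIT results", and that this runs "up to the end of the passive follow-up period (Baseline + follow-up years 1-3 + 3 years passive follow-up) for a total of 7 years". It sets the aim beside published work on interval CRC after FIT in symptomatic patients, so the quantity sought is a risk following a FIT.

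Objective 6 under Exploratory outcomes gives a narrower window: the assessment "will be examined after study end and during the passive follow-up period (Y4-Y7) in a subset of LS patients", restricted to those who were FIT-negative at baseline and in Years 1-3. Table 3 likewise marks only the Y4-Y7 column for this objective.

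The schedule around these FITs is as follows.

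- **Year 0:** kits are "mailed direct to eligible patients within 7-30 days prior to their next scheduled standard of care (SOC) colonoscopy" (Baseline recruitment).
- **Year 2:** "Mailing of study materials and FIT kits for study participants at Study Year 2 will be sent ahead of their SOC colonoscopy", also in a 7-30 day window (Post-baseline study years 1-3).
- **Years 1 and 3:** Table 1 has a colonoscopy only for a FIT at or above 6 μg/g, so a FIT-negative participant next meets the routine one.
- **After Year 3:** no study FIT. The Background says that "surveillance via colonoscopy is recommended at least once every 2 years (biennially) for LS patients", and Table 2 lists "Date of colonoscopy at baseline and years 1-3 + follow-up years 4-6 for the subset of eligible patients".

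Nothing in the article closes a FIT interval at the next colonoscopy or separates CRCs by the test that preceded them.

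**The concern.** A FIT interval cancer is ordinarily one that appears after a negative FIT and before the next test that could have found it. Here the next test is usually a colonoscopy. Once it has been done, a later CRC bears on that examination at least as much as on a FIT taken before it.

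The Discussion proposes FIT for the years between colonoscopies. The question of interest is therefore what happens after a negative Year 1 or Year 3 FIT, up to the next colonoscopy. A single rate over Y4-Y7, or over the whole span, answers something else: how often CRC occurs in FIT-negative people under continuing colonoscopy. It can err in either direction as a measure of post-FIT risk. Cancers arising after a later colonoscopy add to the numerator, and person-time recently examined by colonoscopy dilutes the rate. It is therefore not even a bound.

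**Working it through.** Objective 6 has no event count, sample size or precision figure, so there is no stated figure to reproduce. The check is a timeline count.

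**Inputs.** FITs at Years 0, 1, 2 and 3, and colonoscopies at Years 0 and 2 (Table 1). Gap L from kit mailing to colonoscopy of 7-30 days, that is 7/365 = 0.019 to 30/365 = 0.082 years. Further colonoscopies at about Years 4 and 6 are *inferred* from biennial surveillance, because Table 1 stops at Year 3.

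**Step 1: time for which a negative FIT is the last test.**

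| Negative FIT | Next colonoscopy | Time with FIT last |
|---|---|---|
| Year 0 | Year 0 | L |
| Year 1 | Year 2 | about 1 year |
| Year 2 | Year 2 (same examination) | L |
| Year 3 | about Year 4 | about 1 year |

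The total is 2 + 2L if the Year 4 colonoscopy falls on the anniversary, and 2 + 3L if it also falls L later. The range is 2 + 2(0.019) = 2.04 to 2 + 3(0.082) = 2.25 years.

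**Step 2: share of person-time after a colonoscopy that followed the last FIT.**

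| Window | FIT-last time (years) | Post-colonoscopy share |
|---|---|---|
| Y0-Y7 | 2.04-2.25 of 7 | 68-71% |
| Y0-Y6 | 2.04-2.25 of 6 | 63-66% |
| Y3-Y7 | 1-1.08 of 4 | 73-75% |
| Y4-Y7 | 0-0.08 of 3 | 97-100% |

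No window suggested by the article removes the mixture, and the Y4-Y7 window leaves out nearly all of the time that belongs to FIT.

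**Step 3: share of CRCs in Y4-Y7.** Events need not follow person-time, because some CRCs are found at the surveillance examination itself. Assume a constant onset of one unit per year, and let s be the fraction found at surveillance colonoscopy. Two years' accrual then surfaces at Year 4 (2s) and again at Year 6 (2s). The rest surface between examinations, 3(1 − s) over three years. Only the 2s found at Year 4 have the Year 3 FIT as their last test. The share that follows a colonoscopy done after the last FIT is

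[2s + 3(1 − s)] / [4s + 3(1 − s)].

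- s = 0: 3/3 = 100%
- s = 0.5: 2.5/3.5 = 71%
- s = 1: 2/4 = 50%

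This counts CRCs found at the Year 4 colonoscopy as inside the window. If they fall outside it, the share is 100% throughout.

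**Step 4: the full span at the same extreme.** If every CRC is surveillance-detected, and cancers found at the baseline examination are set aside, two units surface at each of Years 2, 4 and 6. Those at Years 2 and 4 follow a Year 1 or Year 3 FIT with no colonoscopy between, so 4/6, or two thirds, are FIT-last and one third are post-colonoscopy.

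**The case against.** **The article states no attribution rule.** It speaks of potential interval CRCs, and a full protocol or analysis plan may define them. A reader might infer that every later CRC will be charged to FIT. The text does not say so, and that reading should not be pressed. What remains is that the article itself fixes the population and window. An analysis plan that kept to Y4-Y7 could not recover the Year 1-2 interval. Of Year 3-4 it could recover only the CRCs found at the Year 4 colonoscopy.

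**Person-time is not events.** A reader might also infer that the rate mainly reflects post-colonoscopy cancer. That holds for person-time but is not established for CRCs. Step 3 gives half at one extreme, and step 4 gives a minority over the full span.

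**The later colonoscopies are inferred.** This stands. If the Year 4 examination came six months late, for example, FIT would be the last test for 0.5 of the 3 years in Y4-Y7 (17%). Surveillance stops at 75, so someone enrolled at 72 or 73 may have no Year 4 colonoscopy. Against this, Study design relies on high adherence to colonoscopy, and Table 2 expects colonoscopies in years 4-6.

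**The stakes are limited.** The objective is exploratory, has no target and depends on further funding. The Discussion presents FIT as an addition to colonoscopy, so the CRC rate under both tests is a legitimate description. False negatives in Years 0-3 are also addressed under Objective 3, and the primary specificity analysis is untouched. All of this stands. It bears on priority and does not make the combined rate a measure of risk after a FIT.

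**The split can be made at analysis.** Largely true, since colonoscopy dates are collected. That makes the remedy cheap, but the Y4-Y7 window would still need widening.

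**Conclusion.** The point holds in this form: Objective 6 seeks a post-FIT risk but is fixed so that its rate mixes post-FIT and post-colonoscopy CRC. With biennial colonoscopy on schedule, a negative FIT is the last test for about 2.0-2.2 of the 6-7 years and for 0-3% of Y4-Y7. Some 50-100% of Y4-Y7 CRCs would follow a colonoscopy done after the last negative FIT, depending on how many are found at the Year 4 examination. These figures assume colonoscopies at about Years 4 and 6 and, for the event share, constant onset.

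It is tempting to attach a number of misattributed cancers, using the cumulative incidences in the Background and the roughly 10% positivity expected in Years 1 and 3. The documents do not support one. It would need a gene mix, a constant hazard, full kit return, independent rounds and follow-up of every FIT-negative participant, whereas the article speaks only of a subset.

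The change is worth making before passive follow-up begins. It has no bearing on the primary result.

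**What to change.** Keep the overall CRC rate in FIT-negative participants, described as incidence under combined FIT and colonoscopy surveillance. Add to Objective 6 a split by last test:

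- **FIT interval CRC:** diagnosed after a negative Year 1 or Year 3 FIT, up to and including the next colonoscopy. Person-time runs from that FIT and ends at that colonoscopy. The window must include the Year 1-2 and Year 3-4 intervals. Entry to each should depend on the FIT that opens it, not on later FITs also being negative.
- **Post-colonoscopy CRC:** diagnosed after a colonoscopy that followed the last negative FIT, reported by time since that colonoscopy and by mode of detection.

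Base any statement about risk after a negative FIT on the first figure only. State the same window in Objectives, Objective 6 and Table 3.

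The cost is a rewording and one extra split, with no change to testing, colonoscopy or care. Table 2 already holds colonoscopy dates to year 6. Mode of detection is not listed there and may need one added field, and a window reaching Year 7 would need dates for that year. The real price is statistical: few FIT interval CRCs and a wide interval, for an exploratory outcome whose follow-up is not yet funded.
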